### Study design and setting

3.1

The SZ-NARDS registry is a prospective, multicenter, observational cohort study, scheduled to run from January 1, 2025, to December 31, 2028. This study will be conducted across nine tertiary-level NICUs in Shenzhen, China, selected for their infrastructure, expertise in neonatal critical care, and patient volume to represent a broad spectrum of care in the region. The study protocol is reported in accordance with the Strengthening the Reporting of Observational Studies in Epidemiology (STROBE) guidelines (30) (Supplementary Material 1). An overview of the study design is provided in Figure 1.

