**Figure 1 F1:**
[figure not shown]
Flow chart of the study design, the SZ-NARDS, 2025-2028. Neonates diagnosed with ARDS were enrolled as participants, with clinical measurements and biological specimens collected on day 1, during the acute exacerbation phase (defined by the peak OI), on day 28, and within 24 h before death or initiation of ECMO. Outcome data, including censored cases, will be finalized in 2028 after completing follow-up through clinic visits or phone calls. ARDS, acute respiratory distress syndrome; ECMO, extracorporeal membrane oxygenation; SZ-NARDS, the Shenzhen neonatal acute respiratory distress cohort study; OI, oxygenation index.

Clinical management of patients will remain at the discretion of the local attending physicians according to institutional guidelines, with no study-specific interventions. The study features an open design, allowing for the potential inclusion of additional centers that meet the established criteria during the recruitment period.

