### Recruitment, enrollment, and termination

3.5

Recruitment for the SZ-NARDS cohort study will commence on January 1, 2025, at nine hospitals in Shenzhen, Guangdong Province, China. Enrollment and follow-up will be conducted concurrently, with recruitment continuing until the target sample size is achieved. The cohort will be considered complete once all participants have finished the 3-year follow-up period. Research coordinators will provide eligible parents with a detailed study pamphlet and will conduct face-to-face introductions to the cohort. A flowchart of the enrollment process is presented in Figure 2. A participant's active involvement in the study will cease upon death, guardian withdrawal of consent, or confirmed transfer to a non-participating medical facility where follow-up is not feasible.

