#### Sample size determination and accrual plan

3.6.2

Although this is a descriptive cohort study, a formal sample size calculation was performed for a secondary objective of particular significance: the development of a multivariable prediction model for in-hospital mortality. In accordance with the widely accepted criterion of a minimum of 10 events per predictor variable for logistic regression, and anticipating up to 10 potential predictors, a minimum of 100 mortality events is required. Utilizing a conservative estimated mortality rate of 12.6% as derived from previous studies, it is estimated that a total cohort of at least 794 patients would be required to achieve the desired statistical power. To account for potential incomplete data and to ensure adequate power for other secondary analyses, the target sample size is set at 1,000 patients.

The enrollment target is supported by historical annual NICU admissions across the nine high-volume tertiary centers and by pilot accrual data from the coordinating center. Together, these data indicate feasibility within the planned four-year recruitment window (2025–2028). The enrollment-monitoring framework that will be implemented includes quarterly accrual reviews and formal feasibility assessments at 12 and 24 months. In the event that accrual falls below pre-defined thresholds, pre-specified contingency measures are to be enacted. The following measures are to be implemented: activation of up to 1–3 pre-identified tertiary centers in Shenzhen, Guangdong Province; temporary augmentation of research-coordinator full-time equivalents at underperforming sites to improve case ascertainment and data capture; and structured extension of the recruitment period, subject to steering-committee and ethics-committee approval. These measures are intended to ensure the viability of the study while maintaining methodological rigor.

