### Post-discharge follow-up outcomes

4.2

Primary follow-up outcome: survival status at 36 months corrected age.Secondary follow-up outcomes: NDI, SRM, growth restriction, and loss to follow-up rates (evaluated at the 24- and 36-month assessments).

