### Data management system

5.1

This study will prospectively recruit patients, with recruitment anticipated to conclude in 2028. Data will be stored in the Perinatal Cloud Database, a platform accessible via both desktop and mobile devices. Each participating center and patient will be assigned a unique identification number. The online platform ensures secure data storage, facilitates data export based on specified search criteria, and incorporates a logical validation system that flags missing data, outliers, and inconsistencies. This system is designed to uphold data reliability, integrity, and accuracy, while supporting audit trails, data management, and source data validation. As participating centers utilize heterogeneous Electronic Health Record (EHR) systems, data are manually abstracted by trained research coordinators and entered into the central online Case Report Form (CRF). To ensure data fidelity, this process is supported by a rigorous, multi-tiered quality control and data validation protocol designed specifically to mitigate errors associated with manual entry.

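### Recruitment, study end and outcome finalisation are all placed in 2028, which contradicts following every infant to 36 months corrected age

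*Protocol article*

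**What the plan says.** The protocol article gives these dates and commitments:

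- **Recruitment.** Section 3.5: "Recruitment for the SZ-NARDS cohort study will commence on January 1, 2025". Section 3.6.2 reports "feasibility within the planned four-year recruitment window (2025–2028"), and section 5.1 has "recruitment anticipated to conclude in 2028". Section 3.5 also lets recruitment continue until the target is met, and section 3.6.2 allows it to be extended.
- **Study end.** Section 3.1: the study is "scheduled to run from January 1, 2025, to December 31, 2028".
- **Data finalisation.** Figure 1 caption: "Outcome data, including censored cases, will be finalized in 2028 after completing follow-up through clinic visits or phone calls".
- **Follow-up.** Section 3.8.3 sets visits at 6, 12, 18, 24 and 36 months corrected age. The primary follow-up outcome in section 4.2 is "survival status at 36 months corrected age". Section 3.5: "The cohort will be considered complete once all participants have finished the 3-year follow-up period".

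Neurodevelopmental impairment (NDI) is defined at 36 months. Severe respiratory morbidity (SRM) and growth restriction are evaluated at 24 and 36 months, and the long-term prediction models in section 6.2 use the same two ages.

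**The concern.** Recruitment and the study as a whole occupy the same four calendar years, but each survivor needs a further three years of observation, counted from term-equivalent age. An infant enrolled in December 2028 cannot be 36 months old before December 2031. The 2028 end and finalisation dates therefore cannot coexist with recruitment into 2028 and complete three-year follow-up.

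If the 2028 dates were applied as written, the primary follow-up outcome, the 36-month secondary outcomes and the long-term prognostic models would rest on a minority of the cohort. The rest would be missing because of the calendar, not because families dropped out. The Discussion presents long-term follow-up as one of the study's main strengths, so the dates need to support it.

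**Working it through.** **The plan's own figure.** Section 3.6.2 uses 10 events per predictor, 10 predictors and 12.6% mortality: 10 × 10 / 0.126 = 793.65, rounded up to 794. This matches. It concerns in-hospital mortality, so the follow-up dates do not affect it.

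**Inputs.** Start 1 January 2025 and end 31 December 2028 (section 3.1), a span of 1,461 days. Final visit at 36 months corrected age, 36 × 30.4375 = 1,095.75 days. Target 1,000 (section 3.6.2). All gestational ages are eligible (section 3.6.1). The article gives no accrual curve, so even accrual is an assumption, and enrolment is taken to be at birth.

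**Share able to reach 36 months by 31 December 2028.** For gestational age GA in weeks:

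share = (1,461 − 1,095.75 − 7 × (40 − GA)) / 1,461

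- 40 weeks: 365.25 / 1,461 = 25.0%, about 250 of 1,000
- 32 weeks: 309.25 / 1,461 = 21.2%, about 212
- 28 weeks: 281.25 / 1,461 = 19.3%, about 193

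Each count treats the whole cohort as having that gestational age. For the 24-month visit in term infants the share is (1,461 − 730.5) / 1,461 = 50%.

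**Sensitivity to accrual (term infants).**

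- Linear ramp-up from zero over four years: (1/4)² = 6%
- Linear decline to zero over four years: 1 − (3/4)² = 44%
- Target met evenly in three years: 1/3 = 33%
- Target met evenly in two years: 1/2 = 50%

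Only completing recruitment within about the first year would let every term infant reach the visit.

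**Survival status.** An infant who dies before the lock has a known 36-month status. Taking 12.6% mortality, all of it early, the determinable share under even accrual is 0.25 + 0.75 × 0.126 = 34%.

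**Survivors assessable for NDI, SRM and growth.** 250 × (1 − 0.126) = 218 at term and 193 × (1 − 0.126) = 169 at 28 weeks. That is about 170–220 of 1,000 before any loss to follow-up.

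**Why the known statuses cannot simply be analysed on their own.** Under the same assumptions the determinable group would hold 126 deaths among 344.5 infants, or 36.6%, against 12.6% in the cohort. Early deaths are all counted, while most survivors are not.

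**Date needed for complete follow-up.** A term infant enrolled on 31 December 2028 reaches 36 months at the end of 2031. One born then at 28 weeks does so 12 weeks later, in early 2032.

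**The case against.** The best reply is that the protocol intends complete follow-up. Section 3.5 says so, the Figure 1 caption places finalisation after follow-up, and the Discussion says funding covers the three-year assessments. This stands. A reader might infer that most infants are to be left unobserved by design; the documents do not support that. They show end dates that do not fit a stated commitment.

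Other stronger readings also fail:

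- **A quarter as a ceiling.** It holds only under even accrual over the full window. Section 3.5 stops recruitment once the target is reached, so a fast start would raise the share and a slow one would lower it.
- **Infants enrolled after 2025 add nothing on survival.** Those who die before the lock have a known status.
- **Logistic regression with multiple imputation is the only method on offer.** Section 6.1 also lists complete-case analysis, k-nearest-neighbour imputation and inverse probability weighting, and section 6.2 adds further algorithms. The Figure 1 caption mentions censored cases. Handling of censoring may properly sit in an analysis plan that is not shown.
- **Time-to-event analysis is needed in every case.** If all infants are followed to 36 months, survival at that age is a legitimate binary outcome.

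None of this makes the dates compatible. Recruitment would have to finish in about 2025, whereas section 3.6.2 schedules feasibility assessments at 12 and 24 months. The only extension it describes is of recruitment, which would widen the gap.

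**Conclusion.** The dates are wrong as written and must be reconciled. The contradiction itself needs no assumption; it follows from the stated dates and the 36-month visit.

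Its size does rest on assumptions. With even accrual over 48 months and a lock on 31 December 2028, about 25% of term infants and 19–21% of those born at 28–32 weeks could reach the visit, and the other accrual patterns examined give about 6% to 50%. The figures of 34% with determinable survival status and 170–220 assessable survivors also assume 12.6% mortality occurring early. The 28-day primary in-hospital outcome, the other in-hospital outcomes and the 794/1,000 calculation are not undermined.

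**What to change.** Keep 2028 as the close of recruitment and the in-hospital data lock, allowing for the 28-day window of the last infants enrolled. Correct section 3.1 and the Figure 1 caption so that the end of study and the final follow-up lock fall at the last infant's 36-month corrected-age visit, about the end of 2031 to early 2032 if the full window is used. This agrees with section 3.5. Any extension of recruitment under section 3.6.2 should move the follow-up lock by the same amount.

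If the 2028 lock is kept instead:

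- State that 36-month NDI, SRM and growth are analysed only in infants enrolled early enough to reach that visit, and give the reduced number.
- Do not impute these outcomes for infants cut off by the calendar.
- Analyse survival as time-to-event with administrative censoring.
- Amend the completion rule in section 3.5 to match.

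The first route costs a date amendment in the protocol and, where the same dates appear, the registration. By the article's own account the follow-up is already committed and funded. The second route costs most of the 36-month sample.

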### Safety evaluation

3.7

As this is a non-interventional, observational study, participants will only receive standard clinical care. No study-specific procedures that pose additional risks are planned. Therefore, adverse events directly attributable to study participation are not anticipated. All clinical events and complications will be recorded as part of the routine data collection to characterize the natural history of the disease.

### Data collection

3.8

All data variables for the study are summarized in Table 1, with the study timeline illustrated in Figure 3.

**Table 1 T1:** Details of measurements in the SZ-NARDS cohort study.

Phrase	Measurements
NICU Characteristics	Bed capacity, annual NICU admissions, availability of cardiac surgery, presence of in-house ICU physicians, ICU fellowship training programs, trauma care services, ECMO capabilities, high-frequency oscillatory ventilation (HFOV), respiratory therapists, burn care services, and point-of-care blood gas analysis.
Demographic data	
Guardian Information Perinatal information Neonatal characteristics	Age, gender, ethnicity, identification number, phone number, WeChat^a^ contact, home address, marital status, socioeconomic status, and educational attainment.
	Gravidity, parity, type of pregnancy, gestational weight gain, pre-existing maternal conditions, pregnancy-related complications, and treatments received.
	Gestational age, birth weight, gender, mode of delivery, multiple birth status, Apgar score, birth hospital, transport method, transfer duration, umbilical artery blood gas results, and admission temperature.
Baseline (day 1)	Physical examination Neonatal illness severity scores: SNAP-II, SNAPPE-II, NCIS Comorbidities: bacterial infection, systemic inflammatory response syndrome (SIRS), sepsis, severe sepsis, septic shock Laboratory tests: umbilical artery blood gas, complete blood count, CRP, PCT, standard blood gas analysis, lactate, liver and renal function tests, electrolytes, lipids, glucose, coagulation profile Microbiological cultures: blood, midstream urine (if urinary tract infection suspected), stool, sputum, and optional tracheal aspirate Imaging: chest x-ray, lung ultrasound, cranial ultrasound, echocardiography, and non-invasive cardiac function assessments Ventilation and treatment data: respiratory support parameters and pharmacologic interventions Biological specimens for DNA analysis: plasma (1–1.5 ml; from peripheral/cord blood), urine (1–1.5 ml), stool, sputum, breast milk, and optional tracheal aspirate (all stored at –80°C)
In-Hospital Follow-Up (At the most critical phase, Day 28, and within 24 h before death or ECMO initiation)	Identical to baseline measurements: physical examination, illness severity scores (SNAP-II, SNAPPE-II, NCIS), comorbidities, laboratory tests, microbiological cultures, imaging, ventilation/treatment data, and biological specimens.
Post-Discharge Follow-Up (Up to 36 months)	For deceased infants: date and primary cause of death For survivors: occurrence of major complications (e.g., severe neurodevelopmental impairment, chronic respiratory morbidity, growth restriction) For lost cases: date and reason for loss to follow-up

aEEG, amplitude integrated electroencephalogram; ARDS, acute respiratory distress syndrome; CRP, C-reactive protein; CT, computed tomography; ECMO, extracorporeal membrane oxygenation; HFOV, high-frequency oscillatory ventilation; MRI, magnetic resonance imaging; OI, oxygenation index; PBMC, peripheral blood mononuclear cells; PCT, procalcitonin.

a Wechat (Tencent Inc., Shenzhen, China) is a widely used social communication application in China, functionally similar to WhatsApp.

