#### Inclusion and exclusion criteria

3.6.1

Neonates will be enrolled consecutively upon meeting the full set of Montreux criteria for the diagnosis of NARDS during hospitalization. This cohort will include infants of all gestational ages, including premature infants, provided their respiratory distress meets all five Montreux criteria. These criteria include: (1) an acute onset of symptoms within one week following a known or suspected clinical insult; (2) exclusion of respiratory distress attributable to neonatal respiratory distress syndrome (NRDS), transient tachypnoea of the newborn (TTN), or congenital anomalies; (3) radiological evidence of bilateral, diffuse irregularities, including reduced translucency or opacities, that cannot be explained by conditions such as pleural effusion, atelectasis, NRDS, TTN, or congenital anomalies; (4) absence of congenital heart disease as the cause of pulmonary oedema, with echocardiographic confirmation required to verify the origin of the oedema; and (5) the presence of an oxygenation deficit, categorized by the OI as mild (4 ≤ OI < 8), moderate (8 ≤ OI < 16), or severe (OI ≥ 16). All five criteria must be fulfilled for diagnosis.

Exclusion criteria include: (1) respiratory distress due to primary surfactant deficiency (e.g., hyaline membrane disease), TTN, or congenital lung malformations; (2) congenital heart disease resulting in pulmonary oedema; (3) known genetic syndromes or chromosomal abnormalities; (4) data that did not conform to the Montreux criteria or cases with unavailable outcome data; and (5) abandonment or death occurring within 24 h of birth.

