### Statistical analysis plan

6.1

Continuous variables will be summarized as mean ± standard deviation (SD) or median with interquartile range (IQR), depending on distribution. Categorical variables will be presented as frequencies and percentages. Group comparisons will be conducted using the student's *t*-test or Mann–Whitney *U* test for continuous variables, and the *χ*² test or Fisher's exact test for categorical variables.

Univariate logistic regression will be used to examine associations between NARDS and study outcomes. Multivariable logistic regression will then be performed to identify independent predictors. Missing data will be addressed primarily using multiple imputation by chained equations (MICE), assuming data are missing at random. Variables with excessive missingness will be excluded according to predefined thresholds, and the imputation model will be structured accordingly. Sensitivity analyses will include complete-case analysis, k-nearest neighbors (k-NN) imputation, and inverse probability weighting to evaluate the robustness of findings to loss to follow-up. A two-sided *p* < 0.05 will be considered statistically significant. All analyses and visualizations will be conducted using R software (version 4.3.3).

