### Model evaluation and validation

6.3

Model performance will be evaluated using the area under the receiver operating characteristic curve (AUROC), sensitivity, specificity, calibration plots, Brier score, and, where applicable, precision–recall curves for imbalanced outcomes. Internal validation will be performed using a robust strategy: randomly partitioning the cohort into a 70% Discovery Set and a 30% Internal Validation Set at baseline. The validation set will serve as an independent internal check for model generalizability. We will also perform internal validation using cross-validation and bootstrap resampling, strictly adhering to the TRIPOD reporting guidelines for predictive models (38). Where feasible, temporal or center-level external validation (or internal holdout by center) will be undertaken to assess generalizability.

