### Control of confounding and subgroup analyses

6.5

Multivariable models will adjust for key covariates (gestational age in completed weeks, birth weight z-score, sex, major comorbidities). We will perform stratified analyses by gestational age (<32 weeks, 32–36 weeks, ≥37 weeks) and present both adjusted and stratified effect estimates. To address prematurity as a potential source of confounding and misclassification (NRDS vs. NARDS), the central adjudication committee will review all ambiguous preterm cases, evaluating the timing of respiratory failure onset, radiographic features, surfactant exposure/response, and clinical course. For non-randomized treatment comparisons (e.g., ventilation strategies, surfactant use), we will use propensity score methods (matching, inverse probability weighting) and, when appropriate, instrumental variable approaches to reduce treatment selection bias. Sensitivity analyses will include restriction to term infants and to preterm strata to evaluate effect modification by prematurity.

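### The random 70/30 split is not kept within families, so enrolled siblings can fall on both sides of a validation set that the protocol calls independent

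*Protocol article*

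**What the plan says.** **Who enters.** Section 3.6.1: "Neonates will be enrolled consecutively upon meeting the full set of Montreux criteria". The next sentence adds: "This cohort will include infants of all gestational ages, including premature infants". None of the inclusion or exclusion criteria restricts enrolment to one infant per pregnancy or per mother.

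**What is recorded.** Table 1 in section 3.8 lists "multiple birth status" among the neonatal characteristics and the type of pregnancy among the perinatal items. It also lists a guardian identification number, telephone number and address. The statistical sections use none of these.

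**How models are validated.** Section 6.3 describes "randomly partitioning the cohort into a 70% Discovery Set and a 30% Internal Validation Set at baseline" and continues: "The validation set will serve as an independent internal check for model generalizability". Section 6.4 repeats a random 70%/30% division for biomarker discovery and again calls the 30% part independent. Section 6.3 also plans cross-validation and bootstrap resampling without naming a grouping. Validation by time or by centre, including a holdout by centre, is planned only if feasible. The unit of the split, infant or pregnancy, is not named in either section.

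**The concern.** A held-out set checks generalizability only if its members are unrelated to those that trained the model. Co-twins share the mother, the maternal history and the gestational age, usually the centre, and often the perinatal insult. They also share all (monozygotic) or about half (dizygotic) of their segregating genetic variation. If one twin trains the model and the other tests it, a flexible classifier can gain from having already seen a near-copy of the test infant. That gain would not carry over to a new family.

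What is at stake is a headline result. Section 4.3 makes a primary biomarker outcome of a baseline proteomic or metabolomic signature with AUROC above 0.85 for severe NARDS within 72 h, and section 6.4 evaluates such models in the 30% set. Section 6.3 makes its partition at baseline. Once models have been fitted and scored on a split, redrawing it compromises the validation, so the unit should be settled first.

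**Working it through.** **The plan's own figure.** Section 3.6.2 asks for 10 events × 10 predictors = 100 deaths at 12.6% mortality: 100 / 0.126 = 793.65, rounded up to 794. This matches the stated minimum. The target is 1,000, so the validation set is 0.30 × 1,000 = 300 infants.

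**Chance that a pair is separated.** With infant-level assignment, one twin goes to discovery and the other to validation with probability 2 × 0.7 × 0.3 = 0.42. With assignment by pregnancy the probability is 0.

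**How many validation infants are affected.** Let f be the share of the 1,000 infants who have an enrolled co-twin. The documents do not give f, so the range is an assumption. Pairs = 1,000 × f / 2, separated pairs = 0.42 × pairs, and each separated pair puts one infant into the 300.

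| f (assumed) | Pairs | Separated pairs | Share of the 300 |
|---|---|---|---|
| 2% | 10 | 4.2 | 1.4% |
| 5% | 25 | 10.5 | 3.5% |
| 10% | 50 | 21 | 7% |
| 20% | 100 | 42 | 14% |

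**A ceiling on the AUROC gain.** Suppose the true AUROC is 0.85, affected infants make up a share p of both cases and non-cases, and every affected infant is ranked perfectly because of the co-twin. A share 1 − (1 − p)² of case/non-case comparisons is then lifted from 0.85 to 1, a gain of [1 − (1 − p)²] × 0.15.

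- p = 1.4%: (1 − 0.986²) × 0.15 = 0.004
- p = 3.5%: (1 − 0.965²) × 0.15 = 0.010
- p = 7%: (1 − 0.93²) × 0.15 = 0.020
- p = 14%: (1 − 0.86²) × 0.15 = 0.039

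Perfect ranking is extreme, and realistic leakage would be less. The ceiling depends on the equal spread over cases and non-cases, and would be higher if the affected infants were concentrated among the cases.

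**Effect on precision, for scale only.** For a mean or a pregnancy-level covariate, the design effect is 1 + f × ICC. At an assumed ICC of 0.5, f = 2% to 20% gives standard-error multipliers of √1.01 = 1.005 to √1.10 = 1.049, and the minimum of 794 becomes 802 to 874, still below 1,000. For a covariate that differs within pairs, the effect can go the other way.

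**The case against.** The strongest reply is that this is a condensed article. The full analysis plan may name the unit of the split, the folds and the bootstrap, and such details are commonly left to it. The pair count is also unknown and may be small: both siblings must meet all five Montreux criteria, with NRDS and TTN excluded, for a condition that the introduction puts at about 1.5% prevalence. Biospecimens are a voluntary sub-study with separate consent (section 3.8.2), so fewer pairs can straddle the omics split. A holdout by centre would usually keep siblings together.

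Much of this stands, and it limits the size of the point. It does not remove it. The article describes a random partition of the cohort and asserts that the held-out part is independent. As described, the partition does not secure that property when siblings can enrol. The centre-level holdout is conditional and cannot be relied on as the remedy. Voluntary consent lowers the number of pairs, but if a family decides for both twins together, the affected share need not fall.

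A reader might go further and infer three things that the document does not support:

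- **That the regressions ignore the pairing and so give standard errors that are too small.** Section 6.1 says only: "Multivariable logistic regression will then be performed to identify independent predictors". It names no variance estimator, and its silence does not show that infants are treated as independent.
- **That related pairs enter the genome-wide analysis unhandled.** Sections 2.2.3 and 4.3 state its aims and describe no model or sample quality control, so there is no stated method to fault.
- **That the sample size is undermined.** Over the range shown, it is not.

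**Conclusion.** The point holds in a limited form. As written, the 70/30 division can place siblings on both sides of a validation set described as independent. If assignment is by infant, 42% of co-enrolled pairs would be separated. If 2% to 20% of infants have an enrolled co-twin, 1.4% to 14% of the 300 validation infants would have a co-twin in discovery. Any bias in the validation AUROC would be upward and modest: at most about 0.01 to 0.02 for 25 to 50 pairs under the extreme assumption above. The omics classifiers are the most exposed.

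This rests on two assumptions: the share of co-enrolled siblings, which the document does not give, and an infant-level split, which is the plain reading of a random partition of the cohort but is not stated in so many words. Bias also requires that co-twins resemble each other in both features and outcome. It is a minor improvement to the validation and does not threaten the study.

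**What to change.** State in sections 6.3 and 6.4 that the 70/30 split, the cross-validation folds and the bootstrap samples are drawn by mother (or pregnancy), so that siblings always stay in the same set. Grouping by mother also covers a second pregnancy during the multi-year recruitment. Where assignment is made at enrolment, a later-enrolled sibling takes the set of the first. Report the number of co-enrolled siblings in each set.

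The cost is one grouping variable. Table 1 already collects what is needed to build it. Because section 3.4 keeps identifiers apart from the clinical data, authorized site staff would need to derive a coded family number and pass only that to the analysts. The set sizes may depart from an exact 70/30 by a few infants. There is no other material downside, provided that the change is made before the split is drawn.
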